#### Confidentiality {27}

Participant confidentiality and privacy will be strictly held in trust by the study team. This confidentiality will be extended to the data being collected as part of this study. Data that could be used to identify a specific study participant will be held in strict confidence within the research team. No personally identifiable information from the study will be released to any unauthorized third party without prior written approval from the ethical oversight boards that will be overseeing the study.

Data will be collected and stored in password-protected HIPAA-compliant cloud-based systems (REDCap, OneDrive, and Box), with access restricted to study team members who need access to the data to fulfill their job duties. Most data will be captured electronically. Any data that are collected initially on paper or non-digital format will be locked in a file cabinet within a key-accessed office at SCF or UAMS. Confidentiality of participant data for the trial will be ensured by de-identification of child-level data using the HASH ID deidentification process. The PIs will ensure all mechanisms used to share data will include proper plans and safeguards for the protection of privacy, confidentiality, and security for data dissemination and reuse (e.g., all data will be thoroughly de-identified and will not be traceable to a specific study participant). The adequacy of the Research Data Security Plan will be evaluated and approved by SCF and UAMS. Any publications or presentations that result from this research will not identify any subjects individually and will present data in aggregate form only.

#### Plans for collection, laboratory evaluation and storage of biological specimens for genetic or molecular analysis in this trial/future use {33}

Not Applicable. There will be no collection of biological specimens in this trial.

### Statistical methods

#### Statistical methods for primary and secondary outcomes {20a}

For analysis of the primary outcome (proportion of referred children who receive specialty follow-up within 60 days of screening date), the intention-to-treat (ITT) population will be all children referred for follow-up during their school’s hearing screening period, over Years 3–5, regardless of whether their parent/guardian opts in to the specialty telehealth follow-up intervention.

Child-level outcomes will be analyzed using generalized estimating equations (GEE) in order to accommodate correlation within schools that is expected to arise due to the repeated cross-sectional data obtained over time. Moreover, the GEE approach will estimate population-averaged intervention effects that are relevant to public health implementation (50, 51). More specifically, binary outcomes at the child level will be analyzed assuming a binomial outcome distribution and will include the following terms: an indicator for whether the school (i.e. cluster) is observed under the usual care or intervention condition during the cluster-period; time effects to account for the potential confounding effect of time, fixed effects for the variables used in the constrained randomization procedure; and pre-specified adjustment for sociodemographic characteristics (e.g. age, gender, race, ethnicity, and free-reduced lunch eligible) of children to account for potential confounding.

Results will be reported on the relative scale as risk ratios, and absolute effects will be reported as risk differences, both with 95% confidence intervals (52). To do this, the identity and log-link will be used to estimate absolute and relative effects, respectively. In the event of issues with convergence of either the log-binomial or identity-binomial GEE models, we will use the modified-Poisson approach with log or identity link, as needed. If further convergence issues arise with the log-link, we will instead use the standard logit-binomial GEE and report odds ratios as the estimate a relative effect, and if further convergence issues arise with the identity link, the Gaussian distribution will be used with identity link to estimate absolute effects. Standard errors will be estimated using the robust sandwich variance estimator using appropriate small-sample corrections to obtain valid standard errors (53). The GEE estimation approach assumes that data are missing completely at random (MCAR), thus this assumption will be checked. ICC will be calculated to quantify the extent to which outcomes vary by school.

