Using an expected referral rate of 15%, estimation of median cluster size revealed that 3 of the smaller schools may have zero referrals. Among the remaining 22 of 25 schools that are expected to have referrals, we anticipate a median cluster size of 14 referred children and a CV of cluster size of 0.59. For simplicity, we also assumed an equal number of schools per sequence (11 schools). Regarding the rationale for our assumed proportion of referrals resulting in specialty telehealth follow-up within two months, we note that in our prior trial we observed a 42.2% percentage point difference in number of children seen for specialty follow-up within 60 days of screening (25, 28). To be conservative, we assumed the proportion with specialty follow-up to be 20% for children in the control condition and an expected 40 percentage point difference in follow-up between treatment and control conditions. We estimated a within-period intracluster correlation (ICC) of 0.30, based on the results of our prior trial and conservatively assumed a cluster autocorrelation (CAC) of 0.7 with a two-period decay (i.e., nested exchangeable) structure between measurements within the same cluster over subsequent time periods. We assume a two-period decay structure in the design phase rather than an alternate less realistic structure such as exchangeability to protect against an underpowered trial (45,46). With these assumptions, and an alpha of 0.05, the trial will have greater than 90% power to detect an increase of at least 40 percentage points in the proportion of referred children receiving specialty follow-up (comparable to the 42-percentage point difference seen during the prior trial) (46–48).

A sensitivity analysis was performed to assess the effect of changes in assumptions for referral rate, within-period ICC, and cluster autocorrelation (CAC) on power for the primary outcome analysis (Figure 6). Using 80% power as minimum target power (and 90% as preferred power level), the plots show acceptable power in all scenarios.

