**Figure 6 F6:**
[figure not shown]
Sensitivity Analysis for Primary Effectiveness Outcome Assumptions: Screening rate: 90%; Control follow-up rate: 20%; Intervention follow-up rate: 60%. Screening K-5 in Region 1; Screening K, 1, 3, 5, 7, 10 in Regions 2 and 3. Number of clusters, median cluster size, and CV of cluster size dependent on referral rate.

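### If both log-link models fail to converge, the plan swaps the promised risk ratio for an odds ratio on the primary outcome (minor)

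*Protocol article*

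**What the plan says.** The protocol article, Statistical methods for primary and secondary outcomes {20a}, sets the effect measures without condition: "Results will be reported on the relative scale as risk ratios, and absolute effects will be reported as risk differences". Each scale has its own GEE and its own order of fallbacks.

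| Step | Relative effect | Measure | Absolute effect | Measure |
|---|---|---|---|---|
| First choice | binomial, log link | RR | binomial, identity link | risk difference |
| First fallback | modified Poisson, log link | RR | modified Poisson, identity link | risk difference |
| Second fallback | binomial, logit link | **OR** | Gaussian, identity link | risk difference |

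The bold cell comes from this wording: "we will instead use the standard logit-binomial GEE and report odds ratios as the estimate a relative effect". The section gives no step that turns the OR into an RR.

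The model is adjusted. Besides the intervention indicator and time it carries "fixed effects for the variables used in the constrained randomization procedure" and child-level sociodemographic characteristics.

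For planning, Sample size {14} states: "we assumed the proportion with specialty follow-up to be 20% for children in the control condition and an expected 40 percentage point difference". The caption of Figure 6 gives the same pair: "Control follow-up rate: 20%; Intervention follow-up rate: 60"%.

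**The concern.** The two columns of fallbacks are not parallel. On the absolute side the plan changes the distribution and keeps the quantity being estimated. On the relative side its last step changes the quantity. Whether the primary outcome is summarised by an RR or an OR would then depend on whether an algorithm converged, not on the question being asked.

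This would matter less for a rare outcome, where the two measures nearly coincide. Here follow-up is expected in 20% of referred children under control and 60% under the intervention. Someone who is told that the relative effect is 6 may take it to mean six times as many children seen, when the same data show three times as many. The adjusted OR has a further drawback: it is non-collapsible, so its value depends on which covariates are in the model even when they are unrelated to allocation. The result would also be harder to compare with trials that report RRs.

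**Working it through.** **1. The plan's own figure: power.** Sample size {14} states that "the trial will have greater than 90% power to detect an increase of at least 40 percentage points". Inputs from that section: 20% versus 60%, "an alpha of 0.05" (sidedness not stated; two-sided assumed), ICC 0.30, cluster autocorrelation (CAC) 0.7, 11 schools per sequence, 14 referred children per school and period, and CV of cluster size 0.59.

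Take three annual periods (Years 3 to 5), fixed period effects and the nested exchangeable correlation. The sequences differ in exposure only in the middle period, so

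Var = (2/11) × b / [1 − a/(b + 3a)], with a = σ² × ICC × CAC and b = σ² × [ICC(1 − CAC) + (1 − ICC)/m].

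- Favourable case: σ² = (0.20×0.80 + 0.60×0.40)/2 = 0.20 and m = 14. Then a = 0.042, b = 0.028, Var = 0.0070 and SE = 0.0837. Power (normal) = Φ(0.40/0.0837 − 1.96) = 99.8%.
- Cautious case: pooled σ² = 0.40×0.60 = 0.24 and m = 14/(1 + 0.59²) = 10.4. Then a = 0.0504, b = 0.0378 and SE = 0.0968. Power (noncentral t, 20 df) = 97.5%.

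Trial design {8} speaks of four periods; with four the range is 98.3% to 99.9%. The claim of more than 90% is reproduced either way. The calculation rests on a difference in proportions, so the choice between RR and OR does not enter it.

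**2. RR and OR at the planning rates.** With control proportion p0 and intervention proportion p1:

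- RR = p1/p0 = 0.60/0.20 = 3.0
- OR = [p1/(1 − p1)] / [p0/(1 − p0)] = (0.60/0.40)/(0.20/0.80) = 1.5/0.25 = 6.0
- OR/RR = (1 − p0)/(1 − p1) = 0.80/0.40 = 2.0

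**3. Sensitivity.**

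| p0 | p1 | Source | RR | OR | OR/RR |
|---|---|---|---|---|---|
| 0.20 | 0.40 | assumed smaller effect | 2.0 | 2.67 | 1.33 |
| 0.20 | 0.50 | assumed smaller effect | 2.5 | 4.0 | 1.60 |
| 0.20 | 0.60 | planning values | 3.0 | 6.0 | 2.00 |
| 0.20 | 0.622 | planned control rate plus the prior trial's 42.2-point difference | 3.11 | 6.58 | 2.12 |
| 0.05 | 0.10 | rare outcome, for contrast only | 2.0 | 2.11 | 1.06 |

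The gap depends on both risks, so an OR cannot be read back to an RR without them. The figures are for unadjusted proportions. The documents do not allow the further shift from covariate adjustment to be computed.

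**The case against.** Much can be said for the plan as written.

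- **The trigger is remote.** A reader might infer that any failure of the log-link model produces an OR. It does not: log-link modified Poisson comes first and still gives an RR. A rough simulation illustrates this. Its inputs were partly assumed: 200 trials, 22 schools, three periods, 20% versus 60%, ICC 0.30, CAC 0.7, about 14 covariate terms, and default settings of one package. The log-binomial GEE almost always failed, but modified Poisson then converged in about 99% of trials with an independence working correlation and about 90% with an exchangeable one. The OR step was therefore reached in roughly 1% to 10%. These figures depend on the invented covariates and the software, but the direction is clear. This objection stands and limits the weight of the point.
- **The absolute measure is safe.** The risk difference is kept at every step, and the sample size is built on it. This stands.
- **The switch is open.** It is prespecified, the result would be labelled an OR, and with no effect both measures equal 1. An OR of 6.0 and an RR of 3.0 describe the same data, so the factor of 2 is not an error in an estimate. This stands.
- **The population-averaged aim is not lost.** A reader might infer that the OR abandons it. Section {20a} attributes that property to the GEE approach, in which effects are averaged over schools, and a logit GEE has it too. Non-collapsibility over covariates is a different matter.
- **No contradiction between scales is shown.** A reader might also infer that the RR and the risk difference will conflict because they come from different models. Separate log and identity models are the plan's first choice, and nothing in the document shows them in conflict.

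None of this explains why the last relative step should give up the promised measure when the model fitted at that step can supply it. Nor is this a detail left to an unseen analysis plan: the article itself fixes the OR as the relative effect.

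**Conclusion.** The point holds and is minor. If, and only if, both the log-binomial and the log-link modified-Poisson GEE fail to converge, the relative effect for the primary outcome changes from an RR to an OR for a numerical reason. At the planned rates that means reporting 6.0 where the promised measure is 3.0. The ratio of the two runs from 1.33 to 2.12 over intervention rates of 40% to 62.2% with a 20% control rate.

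This rests on the planning rates being roughly right and on unadjusted proportions. The probability of reaching the step is small but cannot be fixed from the documents. The risk difference and the power are unaffected, and the validity of the primary comparison is not in question. What is at stake is which relative measure is reported and how it will be read.

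**What to change.** Keep the existing order of models and change only what is reported at the last log-link step:

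1. Fit the logit-binomial GEE as already planned.
2. For every referred child in the intention-to-treat population, keep the child's own period and covariates and predict the risk with the intervention indicator set to 1, then to 0. Average each set to obtain the standardised risks P1 and P0.
3. Report RR = P1/P0 with a 95% confidence interval, either by the delta method on log RR using the small-sample-corrected covariance or by a bootstrap that resamples schools. Name one of the two in advance.
4. Report the OR only as a supplement, if at all, and not as the relative effect.

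This relies on the logit GEE converging, as the plan already does at that step. Making the logit model with standardisation the first choice would be a preference and is not needed. The cost is a sentence or two in the protocol and analysis plan and a little extra post-estimation code. No data, visits or sample size change.

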#### Interim analyses {21b}

No interim analyses are planned for the primary trial outcome. As a result, there are no stopping guidelines.

#### Methods for additional analyses (e.g. subgroup analyses) {20b}

The choice of variables around which to perform sub-group analyses will be informed by results from preliminary qualitative analyses as well as clinical knowledge around factors that are reasonably expected to influence treatment effect heterogeneity (HTE). From a list of potential candidate variables, sub-group analyses will move forward contingent on the presence of substantial variation in that variable present during baseline data collection. Sub-group analyses will be prespecified as part of the detailed analysis SAP. Each subgroup variable will be included as a fixed effect and interacted with the treatment indicator variable. Contrast statements will be used to produce stratified estimates by subgroup. Where possible, covariate ICCs will be calculated for subgroup variables analyzed for HTE.

#### Methods in analysis to handle protocol non-adherence and any statistical methods to handle missing data {20c}

Missing data may occur if referred children move out of the participating regions or receive follow-up care from providers outside our data observation scope. Child-level enrollment date ranges will help us determine if the former has happened, but we cannot track the latter. Therefore, our analysis will assume that if a specialty follow-up visit is not recorded in our data (and the child remains enrolled in a regional school), the visit did not take place. Depending on the pattern of missingness at the school level, we may employ an inverse probability weighting or multiple imputation approach. We will use complete case analysis only if data loss is thought to be missing completely at random (MCAR).

#### Plans to give access to the full protocol, participant level-data and statistical code {31c}

All finalized datasets, protocols, and study materials will be made publicly available upon request with necessary approvals and execution of a formal data use agreement. The PIs will ensure all mechanisms used to share data will include proper plans and safeguards for the protection of privacy, confidentiality, and security for data dissemination and reuse.

### Oversight and monitoring

#### Composition of the coordinating centre and trial steering committee {5d}

N/A. Trial Steering Committee is not applicable for this minimal risk, pragmatic trial.

#### Composition of the data monitoring committee, its role and reporting structure {21a}

N/A. Data Monitoring Committee is not applicable for this minimal risk, pragmatic trial. A DSMP is in place.

#### Adverse event reporting and harms {22}

The PIs and study staff will develop procedures for data collection, data entry, and quality checks. Any data anomalies will be communicated to the site(s) for clarification. Following written standard operating procedures (SOPs), the PIs will verify that data are generated, documented, and reported in compliance with the protocol and the applicable regulatory requirements for Good Clinical Practices (GCP).

No adverse events are anticipated from the intervention. The equipment will be designed for lay-person use, and adequate training and support will be provided. The enhanced hearing screening and specialty telehealth follow-up will introduce no more than ordinary risk that is encountered in routine school hearing screening and follow-up. For qualitative procedures and data collection, no adverse events are anticipated. Should an individual experience any sensitivities during qualitative data collection, study staff will be trained for an appropriate response, including concluding the data collection event early. An iterative process will be put into place to adapt interview questions and study personnel training as needed to address this possible risk.

Any adverse events or unanticipated problems will be documented and reported within 24 hours to the PIs. If required, PIs will report the adverse event or unanticipated problem to the Institutional Review Board (IRB) of record within 7 days and will determine necessary action, from changes to the protocol to cessation of activity, in compliance with IRB oversight.

#### Frequency and plans for auditing trial conduct {23}

Interval quality assurance audits will be conducted to ensure data quality and detection of any erroneous data. Data exports, integrated equipment, and secure cloud-based solutions will be used to ensure collection of high-quality data at each participating school. Site monitoring will also ensure that the rights of human participants are protected, that the reported trial data are accurate, complete, and verifiable, and that the trial is being conducted in compliance with the approved protocol/amendment(s). Monitoring will be conducted using web-based data validation rules and data manager review.

#### Plans for communicating important protocol amendments to relevant parties (e.g. trial participants, ethical committees) {25}

Important protocol modifications will be communicated to the IRB of record, participating communities, trial registration, and the funder. The CAB will guide communication with communities, including relevant school and healthcare entities.

#### Dissemination plans {31a}

This study will comply with the NIH Data Sharing Policy and Policy on the Dissemination of NIH-Funded Clinical Trial Information and the Clinical Trials Registration and Results Information Submission rule. The trial is registered at ClinicalTrials.gov, and results from this trial will be submitted to ClinicalTrials.gov. All abstracts and manuscripts produced from this research will be submitted for review at Southcentral Foundation and other local entities as appropriate. Community dissemination efforts will be prioritized at the end of the trial to communicate study findings to members of each of the involved communities. We will also make our results available to the global scientific community and welcome the input and collaboration of others studying similar scientific questions in this rapidly moving discipline. Overall, the sharing of data generated by this project will be carried out through academic presentations at regional, national, and international scientific meetings, publication in peer-reviewed journals, and local dissemination in the form of presentations at local community townhalls, school programs, and other venues in according with CAB guidance. Layperson summaries of findings will be published in local newsletters and social media. Local dissemination will be directed by the CAB and regional stakeholders. Priority will be placed on making all publications from this work open access to facilitate community accessibility. Final accepted manuscripts will be deposited into PubMed Central in compliance with the NIH Public Access Policy.

## Discussion

The North STAR trial will evaluate a school-based telehealth intervention that has the potential to substantially improve access to specialty hearing care for rural children. Most childhood hearing loss in rural areas is preventable, but access to the necessary specialty care from audiologists and otolaryngologists in rural areas is limited. While school health programs such as hearing screening provide critical access to preventive care for rural children, loss to follow-up is a pervasive problem. Without intervention, hearing loss has broad-reaching implications for educational attainment, vocational opportunities, and quality of life (1, 3–10). Thus, innovations that can connect rural children to specialty follow-up have the potential to address serious lifelong consequences of untreated childhood hearing loss.

This trial is built on key evidence already developed in the state of Alaska, which determined the optimal methods of screening children for hearing loss in environments where ear infections are common, as well as the vital role that telehealth can play in improving follow-up after screening (13, 25, 27, 28). Both the North STAR trial and our preceding trial in northwest Alaska involve inclusive designs that prioritize community engagement and feedback (21, 29). The STAR model was developed directly from community feedback from the prior trial indicating that transition of specialty telehealth follow-up from clinic to a school-based setting will be essential for improving consistent implementation and long-term success of the intervention (19. 29). Based on CAB guidance, the enhanced screening component of the STAR model is not randomized in this trial, as clear evidence was already developed in another region of Alaska indicating the most accurate screening protocols by age (27). This trial will therefore implement the new evidence-based screening protocol in all participating schools prior to rollout of specialty telehealth follow-up. The STAR model will be refined based on community input during the formative phase of this trial, and ongoing feedback will be solicited during the implementation evaluations conducted annually throughout the trial, with predetermined timepoints for adaptation built into the study timeline to accommodate any needed community-informed modifications.

There are limitations to this trial that should be mentioned. This is a pragmatic trial conducted in a real-world setting, with school staff implementing the intervention. While this can pose challenges with fidelity and uptake, it is more reflective of reality for an intervention that is intended to be scaled across school districts and entire states. Our implementation outcomes will be essential for discerning community-level factors influencing success of the intervention. Cluster randomization inherently reduces power compared to a parallel design, but this design choice was necessary because the intervention is intended to be implemented in a school-wide fashion. Another limitation inherent in the study design is that it is not possible to blind participating schools and parents to allocation. A tremendous amount of coordination will be required with participating schools to ensure that they receive STAR equipment, the needed trainings occur, and materials informing parents of the program are provided for school enrollment packets. To mitigate this limitation, the statistical team will be blinded until primary analysis is complete, and allocation will only be revealed to study staff who need the information for logistics of deploying the intervention.

A key focus of the North STAR trial is sustainability. Emphasis will be placed on developing materials to support policy or practice changes identified by state leaders as valuable for facilitating sustained implementation of STAR. The goal of this trial is to develop a feasible, evidence-based model for school-based specialty telehealth follow-up that can be scaled across the state of Alaska and to other rural environments. Importantly, the STAR model has the potential to support not only increased access to specialty hearing care, but also expanded access to care for other preventable health conditions as well, providing a valuable tool for improving health equity for all rural children.

